# Abbreviations

AQ Amodiaquine

AQ/AS3 Amodiaquine + 3 days (doses) of artesunate

AS Artesunate

CDC Centers for Disease Control and Prevention

CE Cost effectiveness

CQ Chloroquine

CTX Cotrimoxazole

DALY Disability adjusted life year

DPT Diphtheria, pertussis, tetanus vaccination

DPT-HepB/Hib Diphtheria, pertussis, tetanus, hepatitis B, *Haemophilus influenzae* type B

vaccination

DSS Demographic surveillance system

EIR Entomological inoculation rate

EPI Expanded Program on Immunization

GAVI Global Alliance for Vaccines and Immunization

G6PD Glucose-6 phosphate dehydrogenase

HCW Health care worker

Hb Hemoglobin

HCS Hemoglobin color scale

Hib *Haemophilus Influenzae* type b

IEC Information, education, communication

IPD Inpatient department

IPTi Intermittent Preventive Treatment for Infants

# ITN Insecticide treated net

KEMRI Kenya Medical Research Institute

Lapdap Chlorproguanil-dapsone

MIC Minimum inhibitory concentration

# MOH Ministry of Health

MUAC Mid upper arm circumference

OPD Outpatient department

OPV Oral polio vaccine

PRP Polyribosylribitol phosphate (capsule of *H. influenzae*)

RCT Randomized controlled trial

RBM Roll Back Malaria

RDT Rapid diagnostic test

# SP Sulfadoxine-pyrimethamine

SP/AS3 Sulfadoxine pyrimethamine + three doses of artesunate

STGG Skim milk, glycerol and glucose

VR Village reporter

WHO World Health Organization

# Executive Summary

# Approximately three quarters of preschool children in eastern Africa suffer from anemia, defined as a hemoglobin (Hb) concentration below 11 g/dL [1]. For children < 5 years of age, the overall incidence of severe malarial anemia (Hb < 5 g/dl) is estimated at 15-60 cases per 1,000 children per year [2]. Other studies have confirmed that the burden of malaria-related anemia falls primarily on infants and young children [3, 4]. Recently, Schellenberg and colleagues, working in an area of Tanzania with a low to moderate level of *Plasmodium falciparum* transmission and a low level of sulfadoxine-pyrimethamine (SP) resistance, demonstrated that by linking intermittent prophylaxis to routine immunization visits through the national Expanded Program on Immunization (EPI), SP could be administered to children at 2,3, and 9 months of age, resulting in a 59% reduction in rates of clinical malaria and a 50% reduction in the rate of severe anemia (Hb<8 g/dl) compared to those receiving placebo[5]. We propose to conduct randomized double blind placebo-controlled trial to estimate the efficacy of Intermittent Preventive Treatment for Infants (IPTi) with SP + three doses of artesunate (AS) (SP/AS3) given in combination with iron supplementation from 2-6 months of age at routine EPI visits on the prevention of clinical malaria, moderate anemia, and severe anemia in the first 12 months of life in an area with intense malaria transmission and near universal ownership of insecticide treated nets (ITNs). The primary objective is to compare the efficacy of iron supplementation and IPTi with one of 3 antimalarial regimens (SP/AS3, chlorproguanil-dapsone (Lapdap), or AQ/AS3) given at routine EPI visits with iron supplementation alone (+ placebo) on the prevention of clinical malaria in the first year of life. Specific secondary objectives are: 1) Compare the efficacy of iron supplementation plus IPTi with one of 3 antimalarial regimens (SP/AS3, Lapdap [chlorproguanil-dapsone], or AQ/AS3) given at routine EPI visits with iron supplementation alone (+ placebo) on the prevention of moderate and severe anemia in the first year of life; 2) Assess the impact of IPTi with the aforementioned regimens on serologic responses to EPI vaccines (Polio, Diphtheria, Tetanus, Pertussus, Hepatitis B, *Hemophilus Influenzae* type B, and Measles; 3) Assess the impact of IPTi with the aforementioned regimens (particularly SP/AS3) on the nasal carriage rates of *Haemophilus influenza* type b; and 4) Compare the efficacy of iron supplementation and IPTi with one of 3 antimalarial regimens (SP/AS3, Lapdap [chlorproguanil-dapsone], or AQ/AS3) given at routine EPI visits with iron supplementation alone (+ placebo) on the prevention of all-cause hospitalization in the first year of life. This trial will generate important public health information on the efficacy of IPTi in preventing anemia and clinical malaria among infants in an area with intense malaria transmission and ongoing prevention efforts through the use of insecticide treated nets. This trial will contribute towards understanding IPTi’s mechanism of action (i.e. through intermittent clearance of parasites vs. a chemoprophylactic effect afforded through the use of an antimalarial with a long half-life). The information gained will be useful to determine the safety of IPTi, and to decide what sort of antimalarials are appropriate for IPTi, and ultimately will help to direct child survival and malaria control policy in African countries. If alternative drug regimes to SP prove effective, that information will be valuable to policymakers as levels of *P. falciparum* resistance to SP rise with increased usage in east Africa.

# Introduction and Background

## The burden of malaria in children

Malaria is a preventable and treatable disease that continues to cause between 700,000 and 2.7 million deaths each year, 75% of which occur among African children < 5 years of age [6]. Malaria and anemia are two of the leading causes of pediatric hospital admissions and mortality in many African countries [7]. Acute febrile illnesses are responsible for 400 to 900 million hospitalizations per year among African children < 5 years of age living in malaria-endemic areas [6], the majority of which are likely due to malaria.

## The burden of anemia in children

Approximately three quarters of preschool children in eastern Africa suffer from anemia, defined as a hemoglobin (Hb) concentration below 11 g/dL [1]. Anemia in early childhood leads to impaired physical growth and mental development, decreased physical fitness and resistance to infections [8-12], increased risk of subsequent obstetric complications in girls[13] and, when blood transfusions are needed, increased risk of HIV infection and other blood-borne pathogens [14].

# Iron deficiency and malaria as risk factors for anemia

Iron deficiency and malaria have been regarded as the predominant causes of anemia among African children. Their relative contribution depends on age, season and geographical area, reflecting local and time-dependent patterns in the availability of iron-containing foods and malaria transmission. Children are at highest risk for either iron deficiency anemia or malarial anemia between 6 and 36 months of age.

In preschool children, iron deficiency predominantly results from a poor dietary intake of iron coupled with rapid body growth. Although hookworm and schistosomiasis may be contributory factors in children in this age range, during infancy the prevalence and intensity of these infections is low in western Kenya: 4.0% for hookworm, and 0% for *Schistosoma mansoni* in children aged <12 months ([name], CDC/KEMRI, personal communication).

For children < 5 years of age, the overall incidence of severe malarial anemia (Hb < 5 g/dl) is estimated at 15-60 cases per 1,000 children per year [2]. In addition, malaria-associated severe anemia is an important cause of hospital admissions in malaria-endemic areas. In one hospital in Malawi, nearly 10% of admissions were for malaria-related severe anemia; the peak prevalence occurred among infants aged 6-11 months (15%) [7]. These rates were lower in children admitted to a hospital in an area not holoendemic for malaria [7]. Other studies have confirmed that the burden of malaria-related anemia falls primarily on infants and young children [3, 4]. Infants enrolled in a cohort study in a holendemic area in western Kenya had a hemoglobin nadir at 9-12 months of age which was 3.0 g/dL below the mean hemoglobin for age among children in non malarious areas [4]. In that same study, nearly one-third of infants 7-12 months of age had moderate or severe anemia (hemoglobin <8 g/dL), and more than three- quarters had some degree of anemia (hemoglobin < 11 g/dL) [4]. Further evidence from this same cohort suggests that infants and young children have a significant risk of anemia even with low density parasitemia, which may not be associated with fever or clinical illness [15]. It is increasingly recognized that in areas with intense malaria transmission the slow insidious process of repeated, often ‘asymptomatic’ (not associated with fever) malaria infections, leads to chronic anemia and is a major cause of severe anemia and malaria-associated death [16].

Together, these data suggest that malaria related anemia is an enormous public health problem in sub-Saharan Africa, that infants bear the greatest burden of this anemia, and that because the anemia is often associated with asymptomatic malaria infection, malaria prevention rather than treatment strategies are essential for combating the problem.

## Possible interventions to combat malaria and anemia in infancy

*Treatment*

The cornerstone of most malaria control programs is the case management of clinical or microscopy-proven malaria. However, data on the efficacy of case management in reducing mortality have been conflicting [17-19].

An alternative strategy to prevent malaria-related morbidity is to treat anemic children for malaria rather than just treating those with febrile illnesses. A recently completed randomized controlled trial (RCT) in Kisumu, western Kenya compared intermittent SP (monthly for 3 months) with or without supervised daily iron therapy (also for 3 months) to placebo for the treatment of mild anemia (7 < Hb < 10.9) in children <3 years of age. The results showed that supervised daily iron was more effective than intermittent SP for the treatment of mild anemia, and that the combination of the two interventions was slightly more effective than iron supplementation alone ([name], Centers for Disease Control and Prevention, personal communication). A second phase of this study (children with 5 < Hb < 10.9) showed that supervised daily iron was superior to supervised twice-weekly iron for the treatment of mild anemia ([name], Centers for Disease Control and Prevention, personal communication).

###### Prevention

Although treatment of anemic children for malaria could have great public health benefits in sub-Saharan Africa, there are enormous operational difficulties in screening children for anemia, as it is not a widely adopted practice. These difficulties, coupled with the near universality of anemia in infants and young children living in malaria-endemic areas of sub-Saharan Africa suggest the need for a preventive rather than a curative or case management approach.

Recognizing this need, trials of malaria chemoprophylaxis have been undertaken in African countries among school-age children. However the population that is often most at risk, children under 5 years of age and especially infants, is not readily accessible through schools or most community programs. At least one operational research project that relied on community health workers to distribute antimalarials was associated with decreased childhood mortality [20]. Unfortunately, community-based chemoprophylaxis programs have been difficult to implement on a wide-scale basis because of the logistic complexity and cost of most regimens. In addition, there is evidence that infants who receive chemoprophylaxis for malaria have a rebound increase in both severe anemia and clinical malaria morbidity once the intervention is stopped [21, 22]. Moreover, increasing concern about rising antimalarial resistance has made routine chemoprophylaxis less appealing. Currently, Kenya does not have a national policy of chemoprophylaxis for children or infants.

Recently, Schellenberg and colleagues, working in an area of Tanzania with a low to moderate level of  *Plasmodium falciparum* transmission and a low level of sulfadoxine-pyrimethamine (SP) resistance, demonstrated that by linking intermittent prophylaxis to routine immunization visits through the national Expanded Program on Immunization (EPI), SP could be administered under direct observation to children at 2,3, and 9 months of age. Two-month supplies of ferrous sulfate were provided to caretakers at the 2-month EPI visit and the 4-month weighing visit (total 4 months of daily iron supplementation) as a daily supplement to be administered in the home. Children receiving intermittent prophylaxis with SP had a 59% reduction in rates of clinical malaria and a 50% reduction in the rate of severe anemia (Hb<8 g/dl) compared to those receiving placebo.[5] In contrast to the increase in clinical malaria that has been observed among children following discontinuation of chemoprophylaxis [21, 22], no rebound effect was seen after discontinuation of SP in rates of clinical malaria or severe anemia. Thus, study investigators were able to demonstrate a clinically and statistically significant decrease in malaria-related morbidity by using an existing public health intervention that serves as a routine contact point for health-workers and children world-wide.

Although the results of this study were impressive, there are several features about its setting in Ifakara, Tanzania, that limit its generalizability to the rest of sub-Saharan Africa. First, the rate of parasitemia among the control group was very low, suggesting that transmission rates during the study period were low. Second, resistance to SP is low in Ifakara. In some other areas of east Africa, rates of resistance of *P. falciparum* to SP are rising or already high. Because many of the drugs that might some day replace SP for both treatment and prevention strategies are likely to have a shorter half-life than SP, it is important to understand whether the chemoprophylactic effect afforded by a long half-life drug such as SP is essential to the success of the intervention. Third, data on the usage of insecticide treated nets (ITNs) were limited in the Tanzania study. It is unclear what the additional benefit of intermittent preventive treatment might be in area with good coverage of ITNs.

Therefore, this innovative, effective, and potentially sustainable approach to anemia reduction (intermittent preventive treatment in infants, or IPTi) needs to be tested in an area with greater malaria transmission intensity, where SP use is already commonplace, and where ITN coverage is high and well measured. In addition, the efficacy of alternative antimalarial drugs in areas with high or increasing SP resistance should be measured.

## Potential alternative drug regimens to SP for IPTi

### Chlorproguanil-dapsone (Lapdap)

Chlorproguanil (Lapudrine*) in combination with dapsone (in development as a fixed combination: Lapdap) has been shown to be efficacious in treating *P. falciparum* malaria in a small study in Kenya (100% cure on day 7) [23], but less efficacious in the treatment of acute uncomplicated falciparum malaria in Thailand where resistance to SP is more common (14% cure rate) [24]. Another study in Kenya found that although clearance of parasitemia was good following both 1- and 3-course chlorproguanil-dapsone treatments (93.4% and 98.0%), re-infection rates were just as rapid as those seen in community surveillance [25]. A trial in pregnant women in Kenya comparing a single treatment course with SP, CQ, or chlorproguanil (1.2 mg/kg) and dapsone (2.4 mg/kg) given as a single dose found that chlorproguanil-dapsone was as effective as SP in clearing initial parasitemia by day 7, but less effective in maintaining parasite clearance by day 28 (67% parasitemic for chlorproguanil-dapsone vs. 19% for SP)[26]. A rise in Hb concentrations was observed in all 3 groups, but was sustained until day 42 only among those women who remained free of malaria parasites. There is evidence that the shorter half-life of chlorproguanil-dapsone may exert less selective pressure for drug resistance than longer-acting drugs like SP [27], and that although it may select for dihydrofolate reductase (DHFR) mutations, it does not select for dihydropteroate synthetase (DHPS) mutations [28]. Therefore, Lapdap is less likely to drive the evolution of highly resistant *P. falciparum* as quickly as other drugs such as SP.

### Amodiaquine

Amodiaquine (AQ) is a 4-aminoquinoline related to CQ. In persons taking AQ as weekly chemoprophylaxis, there have been reports of agranulocytosis and granulocytopenia [29, 30], hepatitis [31, 32], and increases in serum aspartate aminotransferase levels [33]. However, a recent systematic review of studies of AQ for the treatment of malaria found no increase in adverse events when compared with CQ or SP, and found that all adverse events were minor or moderate, and not life threatening [34]. A recently completed 3-country trial in Africa found no cases of clinical hepatitis among children >10 years receiving either AQ or AQ + artesunate, and no other amodiaquine-related serious adverse events, but did find that 6% of children developed neutropenia (neutrophil count <1000/l) and that 60% of children experienced a decline in serial neutrophil counts [35]. In a smaller study involving younger (6-59 month) Tanzanian children, no serious adverse effects of AQ were noted, and no increase in neutropenia was noted when compared with children receiving SP [36].

In some settings with CQ resistance, AQ has been found to be more efficacious than CQ for treatment of malaria [37, 38]. A recently completed trial of AQ given as IPT (not-linked to EPI visits) found that the protective efficacy of AQ + iron supplementation in preventing malaria fevers and anemia was 64.7% and 67.0% respectively [39].

### Amodiaquine or SP in combination with artesunate

A recent multicenter African trial in children found improved efficacy in treating falciparum malaria in two of three countries among those treated with AQ + artesunate when compared with AQ alone [35]. AQ and artemisinins appear to have a synergistic antimalarial effect when examined in vitro [40].Artesunate given in combination with SP has similarly been shown to be effective and safe for the treatment of acute *P. falciparum* infections [41-43]. In addition to increasing the efficacy of SP and AQ, AS has been demonstrated to reduce gametocyte carriage, and substantially reduce the increase in gametocyte carriage often seen in persons treated with SP alone. [41-43].

### Pharmacokinetic differences among alternative regimens

The half-lives of the potential drugs for IPTi are markedly different. For SP, the range for the half-life of sulfadoxine is 100-231 hours (mean 169 hours), and of pyrimethamine is 54-148 hours (mean 111 hours) [44]. For Lapdap, the half-lives of the two components are 12.6 hours (SD 6.3) for chlorproguanil and 24.5 hours (SD 6 hours) for dapsone [45] For AQ, the half life of the parent compound is short (<10 hours), but the half life of its active metabolite, monodestethyl-amodiaquine, is similar to that of chloroquine [40].

Adding AS to either SP or AQ, while likely to improve efficacy in the clearance of parasitemia, will not extend the half-life of the combination beyond that of the primary drug, as the half-life of AS is very short (estimated at 4-11 hours) [46].

By comparing the efficacy of these drug regimens with components that have markedly different half lives, it may be possible to understand the mechanism of anemia prevention shown in the Tanzania study; that is, how much was due to the intermittent clearance of parasites, and how much to the prophylactic effect from the very long half-life of SP. If the effect found in Tanzanian infants was due to the intermittent clearance of parasites by the antimalarial, then one could hypothesize that a drug (or drug combination) with a shorter half-life would be just as efficacious in preventing anemia as SP, given comparable levels of drug resistance. If, however, the effect seen in the Tanzania study was due to a prophylactic effect of SP (given its long half-life), then the shorter acting drug under consideration (Lapdap) for this study may prove less efficacious for the prevention of anemia. It is also possible that the benefits observed in the Tanzania study will not be found in this setting with higher malaria transmission and greater coverage of ITNs. Because the benefits of this novel intervention have not yet been convincingly demonstrated (only one trial completed to date), it is important that a placebo arm be included in the study. All children in the study should benefit from iron sulfate administration in reducing anemia, regardless of the group to which they have been assigned.

### Availability and cost of alternative regimens

Sulfadoxine-pyrimethamine, amodiaquine, and artesunate are available and licensed for use in Kenya. Only SP is widely available in government health facilities. The cost of SP is low – approximately $ 0.08 per adult treatment course. The cost of a pediatric AS treatment course is difficult to determine, but is likely less than $ 2.00 (a full adult treatment course would be about $2). The cost of AQ for an adult treatment dose is approximately $0.15. The cost of Lapdap is less than $0.50. Lapdap is now commercially available in Kenya,.

If any or all of these drugs prove efficacious, wide scale programmatic implementation should be feasible.

Impact of routine antimalarial usage on carriage of *Haemophilus influenzae* type b (Hib)

While the antibody concentration for long-term protection against invasive Hib disease is 1 l/ml, the IgG concentration needed for protection against Hib carriage is 5 l/ml. This is because the mucosal antibodies needed to block carriage are from transudation from serum. Because of this difference in protective thresholds (invasive disease vs. carriage), it is possible that malaria may decrease the immune response to Hib conjugate vaccine to a level that will allow Hib carriage despite protection against invasive disease. If this is the case, the herd immunity achieved by mass vaccination with a conjugate vaccine may not be achieved because there will still be carriage among children in malarious areas. Unvaccinated children or poor responders will still be subject to acquiring invasive Hib disease. For this reason, it is important to measure the effect of malaria and PIPIT on Hib carriage among children.

## Impact of routine antimalarial usage on response routine vaccinations

In order for this intervention to have a programmatic future, it must be convincingly demonstrated that IPTi does not have a negative effect on the development of antibodies to routinely administered vaccinations. This will be achieved by comparing the proportion of infants in the intervention (IPTi) and placebo groups that attain post-vaccination geometric mean antibody titers (GMTs) above a pre-defined protective level for each EPI vaccine.

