# Clinical Procedures

## Enrollment

At enrollment, capillary blood samples will be taken using finger or heel prick and collected into capillary tubes for later determination of antibodies to polio, diphtheria, tetanus, hepatitis B, and Hib.

It will take approximately 15 minutes for mothers of enrolled infants to respond to the enrollment questionnaire, which will be administered face to face by a trained interviewer, and for the capillary blood sample to be obtained.

The mother of each enrolled child will be issued an identity card with a photo of the infant and mother that will be used to confirm identity of the child at both scheduled and unscheduled visits for the duration of the study.

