## Intervention clinic visits

Enrolled infants returning to clinic at 10 weeks will be given study drugs and will be measured for recumbent length, weight, and mid-arm upper arm circumference. Capillary blood samples will be taken using finger or heel prick for later G6PD enzyme level testing. Blood will be collected on filter paper at the 10 week visit for later testing for genetic markers for drug resistance. Infants returning to the clinic at14 weeks will be given the 2nd dose of the study drugs. At the 9-month visit, infants will be given the final dose of the study drugs and a capillary blood sample will be taken for later measles serology testing.

A questionnaire soliciting information about overall health of the baby, febrile episodes, other intercurrent illnesses, use of other medications, ITN usage, and compliance with iron will be administered at each clinic visit. The form will be based on the OPD surveillance form used in the DSS, but will solicit more detailed information. Infants whose caretakers state that their child has been given CTX in the past 2 weeks will either a.) not be given the dose of intervention drug until 2 weeks after CTX was given, or b.) be withdrawn from the study (if CTX is given as a daily dose).

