## Follow-up clinic visits (non study drug administration visits)

Parents will be asked to bring enrolled infants back to the clinic for follow up visits at 18 weeks, and at 12, 18, and 24 months. A compliance monitor will visit the houses of families who fail to appear within 2 weeks of a follow-up visit. To facilitate the work of compliance monitors, a photograph of each mother and child will be made at enrolment, and that photograph kept with a map locating the place of residence. These documents will be returned to the mother at the conclusion of the study or destroyed.

At the 18-week visit, blood (from the same finger prick) will be obtained and frozen at –70C for later determination of post-vaccination serologic testing for antibodies to polio, diphtheria, tetanus, hepatitis B, and Hib. At the 12-month visit, blood will be obtained for determination of sickle cell trait and frozen for later determination of measles antibody titer. Blood will also be collected on filter paper for later testing of genetic markers for drug resistance.

A questionnaire (identical to that administered during the intervention visits) soliciting information about overall health of the baby, febrile episodes, other intercurrent illnesses, use of other medications, ITN usage, and compliance with iron will be administered.

The algorithm for antimalarial treatment of children who are febrile at the 18 week, and at 12, 18, and 24 month visits will be the same as for the intervention visits, with the exception that all infants who need treatment will be provided quinine (18-week visit) or Coartem (12, 18, and 24-month visit if the child weighs at least 5 kg), as no children will be receiving study drugs at these visits. Children weighing less than 5 kg requiring antimalarial treatment will receive quinine. Children with severe malaria will treated with quinine, regardless of age. Infants with Hb<8 g/dl at the 12, 18, or 24-month visits will be treated with iron per the national policy.

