# Laboratory procedures

Thick blood smears made from capillary blood will be stained with 2-3% Giemsa stain (pH 7.2) for 45 minutes and examined for parasites. Parasites and leukocytes will be counted in the same fields until 500 leukocytes are counted. Parasite densities will be estimated using an assumed leukocyte count of 8,000 leukocytes per l of blood. The limits of detection are estimated at <10 parasites/l of blood.

Dried filter papers will be sent to the London School of Tropical Medicine and Hygiene for analysis of molecular markers of resistance. Although capacity exists in Kenya to conduct this analysis, this central reference lab will be used by all study sites for this analysis, to ensure quality assurance and comparability of results across IPTi sites. To further develop molecular analysis capacity at KEMRI/CDC, one laboratory technician from KEMRI/CDC will travel to London to analyze the samples in the central laboratory.

Capillary blood will be collected in a microcuvette and examined in a Hemocue machine to determine the Hb level. Capillary blood will also be collected into a Microtainer tube for sickle cell testing, and EPI vaccine antibody testing. Analysis of serologic response to EPI vaccines will be performed by the Pasteur Institute in France or another comparable laboratory selected by WHO.

Sickle cell testing will be done in Kenya using a standard Hb electrophoresis technique. Testing for glucose-6-phosphate dehydrogenase genotype will be performed by polymerase chain reaction (PCR). For the primary analysis of the immune response to Hib vaccine, concentrations of anti-PRP antibody will be compared in the SP and placebo groups at 18 weeks. As part of the secondary analysis, the immune response to vaccine among children in the placebo group who have symptomatic malaria, asymptomatic malaria, and no malaria will be evaluated.

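### The stated vaccine-antibody analyses leave out the pre-vaccination titres the trial draws; the share above a protective level is a valid measure of protection but may understate a loss of vaccine response

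*Protocol*

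**What the plan says.** The protocol section *Impact of routine antimalarial usage on response routine vaccinations* sets the aim: it has to be shown that "IPTi does not have a negative effect on the development of antibodies to routinely administered vaccinations". It also fixes the method, which is to compare between IPTi and placebo the proportion of infants "that attain post-vaccination geometric mean antibody titers (GMTs) above a pre-defined protective level". A geometric mean belongs to a group, so I read this as each infant's own titre. No rise from an earlier titre is required.

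*Laboratory procedures* states a different primary analysis for Hib: "concentrations of anti-PRP antibody will be compared in the SP and placebo groups at 18 weeks". This has no threshold, but it also uses only the post-vaccination value.

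The trial does draw earlier blood:

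- At *Enrollment*, blood is "collected into capillary tubes for later determination of antibodies to polio, diphtheria, tetanus, hepatitis B, and Hib". The 18-week sample is taken "for later determination of post-vaccination serologic testing for antibodies to polio, diphtheria, tetanus, hepatitis B, and Hib".
- At the 9-month visit, when measles vaccine is due, "a capillary blood sample will be taken for later measles serology testing". At 12 months blood is "frozen for later determination of measles antibody titer".

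The *Study Schedule* table confirms antibody samples at 6 weeks, 18 weeks, 9 months and 12 months. The statistical analysis paragraph under *Data Management* does not cover serology, and no section gives the earlier titres a role. Maternal antibody is not mentioned, and the entry criteria set no limit on titre.

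**The concern.** The aim is about the development of antibody, which is a change. The stated rule measures an end state. An infant who carried a high maternal titre at 6 weeks could still be above the level at 18 weeks whatever the vaccine did. Such infants should be equally frequent in all arms on average, so they pull the arms together. When the aim is to show no harm, that is the unsafe direction.

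The stakes are a secondary objective, but an important one. The protocol makes this demonstration a condition for using IPTi in programmes, and *Justification* expects policymakers to use the vaccine-response data when they judge safety. The information needed to address the problem is already being collected.

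**Working it through.** The protocol gives no expected seroprotection rate, margin, power or maternal-antibody share for serology, so there is no figure of its own to reproduce. All numerical inputs below are assumptions, except the visit times and the two sample sizes.

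**1. Direction.** Let r be the probability that the vaccine alone brings an infant above the level. Let m be the share above the level at the post-vaccination sample from maternal antibody alone. If m is equal across arms and independent of response:

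- P(above level) = m + (1 − m) r
- observed difference = (1 − m)(r₀ − r₁)

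Any m above zero shrinks the observed loss.

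**2. How high an infant must start.** From 6 to 18 weeks is nominally 12 weeks, or 84 days. To stay above the level unaided, the 6-week titre must exceed it by a factor of 2^(12/half-life in weeks). For assumed half-lives of 3, 4, 5 and 6 weeks this is 16, 8, 5.3 and 4. That is demanding, so m can be very small.

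**3. Size of m.** Assume normal log10 titres at 6 weeks. With z the normal quantile of the share above the level at 6 weeks:

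m = Φ( z − (84/half-life) × log10 2 / SD )

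At SD 0.5 and half-life 35 days the second term is 2.4 × 0.301 / 0.5 = 1.445. The last column gives m over SD 0.4–0.6 and half-life 28–50 days.

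| Above level at 6 weeks | z | m | True 10-point loss appears as | m over all assumptions |
|---|---|---|---|---|
| 30% | −0.524 | Φ(−1.969) = 2.4% | 9.76 | 0.3–9% |
| 50% | 0 | Φ(−1.445) = 7.4% | 9.26 | 1–20% |
| 70% | 0.524 | Φ(−0.921) = 17.9% | 8.21 | 4–38% |
| 90% | 1.282 | Φ(−0.163) = 43.5% | 5.65 | 16–67% |

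**4. Effect on a no-harm conclusion.** As an illustration, assume true response of 90% on placebo and 80% on IPTi, a 10-point non-inferiority margin and one-sided 0.025. The protocol sets no margin. The arm sizes are 250 and 379, the malaria figures from *Sample Size*; the number with serology is not stated. The chance of declaring no harm is

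Φ( [0.10 − (q₀ − q₁)] / √[q₀(1 − q₀)/n + q₁(1 − q₁)/n] − 1.96 ), with q = m + (1 − m) r.

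For m = 10%, q₀ = 0.91 and q₁ = 0.82. At n = 250 the standard error is 0.0303, and Φ(0.01/0.0303 − 1.96) = 5.2%. For n = 250 to 379 the chance is:

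- m = 0: 2.5%
- m = 10%: 5–6%
- m = 30%: 20–27%
- m = 50%: 57–75%

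**5. Precision.** Adjusting log10 post-vaccination titre for log10 baseline titre cuts residual variance by r², where r is now the correlation between the two. For an assumed absolute correlation of 0.3–0.5 this is 9–25%. The gain applies to the continuous comparison, not to the proportion above the level.

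**The case against.** Several points on the other side stand.

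- **Share protected is a legitimate endpoint.** An infant protected by any antibody is rightly counted as protected, and randomisation balances maternal antibody on average. A reader might infer that the stated comparison is biased or invalid. It is not; the dilution arises only when the proportion is read as vaccine response.
- **Not everything is scored against a level.** A reader might infer that all vaccine responses are judged by a threshold alone. For Hib, *Laboratory procedures* compares concentrations.
- **Silence is not a decision to ignore the baseline.** The enrolment titres are to be determined, and a statistical analysis plan that is not shown could use them. It remains true that the protocol itself fixes two analyses and both are post-vaccination only.
- **The harm is conditional.** It is tempting to say that a real loss is understated. The documents give no titres, half-life or starting share, so only *may be understated* is supported. The largest figures need 90% of infants above the level at 6 weeks, for which the protocol offers no evidence. The formula also needs maternal antibody to be independent of response.
- **A stricter responder rule is not the answer.** Requiring, say, a fourfold excess over expected decay needs a half-life that the documents cannot supply. At 35 days, an infant starting at 16 times the level is expected at 16/5.3 ≈ 3 times it, so would have to reach about 12 times. A clearly protected infant at 10 times would be scored a non-responder.

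**Conclusion.** The point holds as a mismatch between aim and analysis. The two stated serology analyses do not use pre-vaccination titres that are already scheduled. The proportion above the level remains valid for protection, but may understate a loss of response by the factor (1 − m). Under the assumptions shown, a true 10-point loss would appear as anything from nearly 10 points to about 5.65 in the central case. The effect is probably negligible where few infants start above the level, and could be material where most do. The size cannot be settled from the protocol.

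The case for adjustment is cleanest for the antigens sampled at enrolment, because that sample precedes study drug, which starts at 10 weeks. It is weaker for measles: the 9-month sample comes after the courses at 10 and 14 weeks, so it is not a pre-treatment covariate.

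**What to change.** In *Impact of routine antimalarial usage on response routine vaccinations* and *Laboratory procedures*:

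1. Keep the comparison of the proportion above the protective level.
2. For each antigen with a pre-vaccination sample, add a comparison of log10 post-vaccination titre between each drug arm and placebo, adjusted for the infant's own pre-vaccination log10 titre. Use the enrolment sample for the 18-week antigens and a missing-baseline indicator where no usable sample exists.
3. For measles, report the 12-month comparison adjusted for the 9-month titre as supporting only.
4. Reconcile the two Hib statements: which measure is primary, and which arms are compared with placebo.

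The adjusted comparison needs no assumed half-life. It does not fully separate vaccine antibody from remaining maternal antibody, but it no longer depends on a threshold and it uses the known starting titre. The cost is a change of wording, a little more analysis and the handling of missing baseline samples. No blood or visits are added.
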